**Design:**

This is a multicenter (three centers at the time of  publishing this paper) randomized controlled clinical trial to examine the safety of percutaneous tracheostomy using FB. We will include all consecutive adult patients admitted to the ICU in whom percutaneous tracheostomy for prolonged mechanical ventilation is indicated and with no exclusion criteria for using FB. Eligible patients will be randomly assigned to receive blind PDT or PDT under endoscopic guidance. All procedures will be performed by experienced intensivists in PDT and FB. A Data Safety and Monitoring Board (DSMB) will monitor the trial. The primary outcome is the incidence of perioperative complications.

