#### PDT modality used

PDT will be performed with the single dilatation method, as it is the usual practice in the ICU in La Paz University Hospital. For both arms, the patient will be placed with the neck extended and the usual aseptic measures will be taken in the surgical area. All patients will be monitored with electrocardiographic control, invasive blood pressure, and continuous pulse oximetry. A FiO_2_ of 100% will be maintained throughout the procedure with correct visualization of the curves and parameters obtained from the mechanical ventilator. Sedation and analgesia will be initiated, and if it is already being infused continuously due to its basal situation, an extra dose will be administered if necessary along with a bolus dose of a non-depolarising neuromuscular blocking agent (usually cisatracurium).

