#### Data collection

In addition to demographic variables, and duration of the procedure (from skin incision to placement of tracheostomy tube), we will collect perioperative complications (following the classification proposed by Durbin [28] modified [29]. Minor complications include those that are easily corrected, with no risk of sequelae or need of unscheduled therapeutic strategies for their solution: (a) haemorrhage: bleeding controlled with digital pressure that does not cause hemodynamic instability, nor requires surgical revision or transfusion; (b) transient desaturation: desaturation during the procedure (SpO_2_<90% but ≥ 85%); (c) loss of airway control: failure to secure the airway without impact on SpO_2_ (not <90%); (d) atelectasis: partial atelectasis (segmental or lobar) without a decrease in SpO_2_<90% and that does not require fiberoptic bronchoscopy for its resolution; (e) arterial hypotension, which requires expansion with less than 1000 ml of fluids and does not require administration or increase of previous doses of inotropics; (f) barotrauma: subcutaneous emphysema; (g) rupture of tracheal rings: rupture of the tracheal ring during any phase of the procedure (only in patients in whom endoscopic guidance is performed); and (h) technical problems without clinical repercussions: puncture of the ETT cuff, difficulty in inserting the cannula or impossibility to complete the technique as an isolated complication that did not lead to repercussions such as desaturation or loss of the airway. Major complications include those when an unscheduled therapeutic act was required, or when the complication entails potential risk (although there had been no life threat or consequential sequelae), or there is a real risk to life, cardiac arrest, or death directly related to the complication derived from the technique: (a) hemorrhage: bleeding that causes hemodynamic instability, and/or requires surgical revision, and/or transfusion; (b) desaturation (SpO_2_<85%) of any duration; (c) loss of airway control causing a drop in SpO_2_<85%; (d) total or partial atelectasis that have an impact on SpO_2_ or require a therapeutic maneuver for its solution (fiberoptic bronchoscopy); (e) hypotension that requires treatment with more than 1000 cc of fluids, and/or initiation of vasopressors, or an increase in previous doses; (f) false passage that causes injury to the trachea or mediastinal emphysema or desaturation (SpO_2_ <85%); (g) barotrauma: pneumothorax or mediastinal emphysema; (h) rupture or tear of the tracheal wall; (i) injury to the posterior wall of the trachea: damage produced to the posterior wall of the trachea with the needle, guide, or dilator; and (j) technical problems with clinical repercussions: puncture of the ETT cuff, difficulty in inserting the cannula, or impossibility of completion of the technique that entails consequences such as desaturation or loss of the airway or serious complications that require a change in strategy.

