
We will also collect the arterial partial pressure of CO_2_ at the beginning and end of the procedure, the arterial partial pressure of O_2_ at the beginning and end of the procedure, pH at the beginning and end of the procedure, minimum arterial oxygen saturation (measured by pulse oximetry) during the procedure, and maximum end-tidal CO_2_ during the procedure (if capnography is available).

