#### Statistical analysis plan

Data will be collected in each participating ICU using a standardized form. Then, data will be transmitted to the coordinating center whenever a patient dies or is discharged from the hospital. Before exporting the data into a computerized database at the randomization center, the coordinator ([name]) will check the completeness and the quality of information. Logical checks will be performed for missing data and to find inconsistencies. If necessary, the data collector will contact the investigator by phone to validate the data or reformat the data for entry into the database. Considering that the rate of complications described in published work in which PDT with FB was performed ranged between 3.7% and 16%, and those without FB (eliminating extreme values) ranged between 11% and 25%, for a confidence level of 95%, a statistical power of 80% and a potential loss of 10%, a sample size of 221 patients has been calculated for each arm. Collected data will be anonymized in compliance with the Spanish Law 3/2018, of December 5, on Data Protection and Guarantee of Digital Rights. The results of the quantitative variables will be expressed as mean and standard deviation when they fit a normal distribution curve evaluated with the test of Kolmogorov-Smirnoff. Data without a normal distribution will be expressed as median and interquartile range. Qualitative data will be expressed through its absolute frequency and percentage. The comparison between quantitative variables will be carried out using the Student’s t test or the Mann-Whitney test, depending on the distributions of the variables analyzed. The chi-squared test will be used to demonstrate differences between qualitative variables. No imputation will be made of the lost data. All tests will be considered two-tailed at a 95% level of significance. All statistical analyses will be performed using statistical software SAS Enterprise Guide 8.2 (Cary NC, SAS Institute Inc., USA). Statistical significance will be set at p<0.05.

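### Starting PaO2 is collected but unused: adjusting minimum SpO2 and the primary outcome for it is a cheap efficiency gain, probably 0 to 1 point of power for the primary outcome and more for minimum SpO2

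*Protocol article*

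**What the plan says.** The abstract of the protocol article states the main endpoint: "The primary outcome is the incidence of perioperative complications". The Data collection section lists 8 minor and 10 major complication types. Some are defined by oxygen saturation, for example "transient desaturation: desaturation during the procedure" among the minor ones and any fall below 85% among the major ones.

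The same section records, apart from the complications, "the arterial partial pressure of O_2_ at the beginning and end of the procedure" and "minimum arterial oxygen saturation (measured by pulse oximetry) during the procedure". Minimum SpO2 has no starting value of its own in that list.

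The Statistical analysis plan section fixes the tests. For categorical outcomes: "The chi-squared test will be used to demonstrate differences between qualitative variables". For continuous ones: "The comparison between quantitative variables will be carried out using the Student’s t test or the Mann-Whitney test", chosen by distribution. No covariate is named for any comparison, and missing data are not to be imputed. A fuller analysis plan that is not shown might name covariates.

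**The concern.** Oxygenation before the procedure plausibly predicts who desaturates during it, and the trial already measures it. The protocol itself lists high oxygen requirements among the contraindications to the technique. That supports the direction of the link but not its strength.

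If a measured baseline value predicts the outcome, leaving it out of the comparison gives up precision and leaves chance imbalance between the arms uncorrected. The Background postulates that guidance brings no reduction in complications. A null result would therefore be read through the width of its confidence interval, so precision matters here. The Discussion also names effects on ventilatory parameters as an aim, which gives minimum SpO2 some weight of its own.

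**Working it through.** **1. The plan's own figure.** Inputs from the Statistical analysis plan section: two-sided alpha 0.05, power 80%, loss 10%, rates of 3.7–16% with and 11–25% without bronchoscopy. The pair actually used is not named. With the lower ends, 3.7% v 11% (mean 7.35%):

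n = [1.96·√(2·0.0735·0.9265) + 0.842·√(0.037·0.963 + 0.11·0.89)]² / 0.073² = 199.4 per arm, and 199.4/0.9 = 221.6.

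This matches the stated 221. The pair 10% v 20% also fits (199 per arm; 199/0.9 = 221.1). Either way the size was set for an unadjusted comparison with about 199 evaluable patients per arm.

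**2. Unadjusted power at 3.7% v 11%.** SE = √[(0.03563 + 0.0979)/199] = 0.0259. Power = Φ(0.073/0.0259 − 1.96) = 80.5%.

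**3. Adjusted power.** Assume a standardised covariate x with a given odds ratio per SD on the whole composite, with intercepts set so that the marginal rates p₀ and p₁ stay fixed. The efficient variance of the risk difference is the mean over x of 2m₀(1−m₀) + 2m₁(1−m₁) + [(m₁−m₀) − (p₁−p₀)]², divided by 398. Here m₀ and m₁ are the model risks at x in the two arms.

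| Odds ratio per SD (assumed) | Variance reduction | Power | Equivalent n per arm |
|---|---|---|---|
| 1.25 | 0.3% | 80.6% | 198 |
| 1.5 | 1.1% | 80.9% | 197 |
| 2 | 3.4% | 81.8% | 192 |
| 2.5 | 6.0% | 82.8% | 187 |
| 3 | 8.6% | 83.8% | 182 |

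Example for odds ratio 2: Φ(0.073/(0.0259·√0.966) − 1.96) = 81.8%. A simulation with 3,000 runs per setting gave gains of 0.4 to 3.3 points. At the midpoints of the quoted ranges (9.85% v 18%), power goes from 65.7% to 66.6%, 68.2% and 71.6% for odds ratios of 1.5, 2 and 3. At 10% v 20%, simulation for the same three odds ratios gave 80.2 to 80.7%, 80.8 to 83.2% and 81.0 to 86.0%.

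**4. Dilution in the composite.** Minor (b) and major (b) and (c) require a fall in saturation. Major (d), (f) and (j) can be met with or without one. Bleeding, hypotension, tracheal wall injury and cuff puncture need not depend on PaO2. Suppose PaO2 predicts only the desaturation part of a 15% composite, with the other events independent of it (both assumed):

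| Desaturation share (assumed) | Odds ratio on desaturation: 1.5 | 2 | 3 |
|---|---|---|---|
| 50% | 1.22 | 1.40 | 1.68 |
| 30% | 1.13 | 1.23 | 1.37 |

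Entries are the resulting odds ratios on the composite. Even the largest, 1.68, gives a variance reduction of 1.9% at 3.7% v 11%, and Φ(2.818/√0.981 − 1.96) = 81.2%, a gain of 0.7 points.

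**5. Minimum SpO2.** ANCOVA multiplies the variance by 1 − r². Starting from a nominal 80% power, the new power is Φ(2.80/√(1−r²) − 1.96).

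| r (assumed) | Variance reduction | Power |
|---|---|---|
| 0.1 | 1% | 80.4% |
| 0.3 | 9% | 83.6% |
| 0.5 | 25% | 89.9% |

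In terms of patients, r of 0.3 to 0.5 is worth 1/0.91 to 1/0.75, that is 10% to 33% more.

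**The case against.** The strongest reply is that nothing here is wrong. An unadjusted chi-squared test is valid under randomisation, 221 per arm was sized for it, and covariates are often left to a fuller plan. That stands. A reader might infer that the planned tests are biased or defective, but the documents do not support it.

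A reader might also infer that adjustment would recover substantial power for the primary outcome, or make up for planning rates at which the trial falls short of 80%. It would not. No passage links starting PaO2 to complications, the exclusion of high oxygen needs narrows its range, and the composite is diluted as shown above. At the midpoint rates even an odds ratio of 3 leaves power at 71.6%.

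The covariate is not clearly a clean baseline either. The text fixes the sample only to the start of the procedure, and procedure duration is counted from skin incision. The arms already differ when the tube is repositioned, by bronchoscope in one and by laryngoscopy in the other. A sample taken after that step could carry part of the treatment effect, and adjusting for it could remove some of that effect. The oxygen fraction at sampling is not among the listed data, while "A FiO_2_ of 100% will be maintained throughout the procedure". PaO2 is hard to interpret as reserve without it. This objection stands and shapes the fix, which is therefore not a change of analysis wording alone.

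Last, minimum SpO2 is not what the trial was sized on, it is bounded and probably skewed, and 80% is only a nominal starting point. The 1 − r² result is an approximation, which is why a rank-based version is offered.

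**Conclusion.** The point holds as a low-cost efficiency improvement of minor importance. For the primary outcome the expected gain is about 0 to 3 points of power at 3.7% v 11% for composite odds ratios of 1.25 to 3 per SD. It is probably 0 to 1 point if PaO2 acts only through desaturation events making up 30% to 50% of the total. The stronger case is minimum SpO2, with a 9% to 25% variance reduction at correlations of 0.3 to 0.5.

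The prognostic strengths, the correlations and the desaturation share are all assumptions; the documents give none of them. The conclusion also requires that the starting sample precede the arm-specific airway step.

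**What to change.** Before any comparison by arm, pre-specify the following:

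- **Minimum SpO2:** ANCOVA on arm and starting PaO2, linear or rank-based according to the distribution.
- **Primary outcome:** keep the chi-squared test. Beside it, report a standardised risk difference with 95% CI from a logistic model on arm and log starting PaO2. The model's odds ratio is conditional, so the risk difference should be the reported effect.
- **Starting sample:** define it as drawn before the first arm-specific airway step, and record the FiO2 at which it was taken.
- **Missing starting PaO2:** fill with the overall mean and add a missing indicator, so that no patient is dropped.

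The cost is an analysis paragraph, a sampling definition and one extra field on the form. The rule against imputation needs an exception limited to this baseline covariate; outcomes stay unimputed. Enrolment began in December 2019, so patients entered before the definition is fixed may have a less clean value. Where the timing of their sample relative to the airway step can be established, record it. Where it cannot, check the adjusted results without those patients' covariate values.

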#### Statistical analysis plan

Data will be collected in each participating ICU using a standardized form. Then, data will be transmitted to the coordinating center whenever a patient dies or is discharged from the hospital. Before exporting the data into a computerized database at the randomization center, the coordinator ([name]) will check the completeness and the quality of information. Logical checks will be performed for missing data and to find inconsistencies. If necessary, the data collector will contact the investigator by phone to validate the data or reformat the data for entry into the database. Considering that the rate of complications described in published work in which PDT with FB was performed ranged between 3.7% and 16%, and those without FB (eliminating extreme values) ranged between 11% and 25%, for a confidence level of 95%, a statistical power of 80% and a potential loss of 10%, a sample size of 221 patients has been calculated for each arm. Collected data will be anonymized in compliance with the Spanish Law 3/2018, of December 5, on Data Protection and Guarantee of Digital Rights. The results of the quantitative variables will be expressed as mean and standard deviation when they fit a normal distribution curve evaluated with the test of Kolmogorov-Smirnoff. Data without a normal distribution will be expressed as median and interquartile range. Qualitative data will be expressed through its absolute frequency and percentage. The comparison between quantitative variables will be carried out using the Student’s t test or the Mann-Whitney test, depending on the distributions of the variables analyzed. The chi-squared test will be used to demonstrate differences between qualitative variables. No imputation will be made of the lost data. All tests will be considered two-tailed at a 95% level of significance. All statistical analyses will be performed using statistical software SAS Enterprise Guide 8.2 (Cary NC, SAS Institute Inc., USA). Statistical significance will be set at p<0.05.

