## Discussion

This is a protocol for a randomized controlled trial designed to evaluate the efficacy of percutaneous tracheostomy under endoscopic guidance versus blind percutaneous tracheostomy (always performed by experienced intensivists) and to evaluate the effects on ventilatory parameters during percutaneous tracheostomy with and without endoscopic control.

National surveys carried out in some European countries showed that the use of FB as part of the technique is used in a heterogeneous way, ranging between 16% and 98%, although the “time” factor in which each of them was carried out has to be taken into account [30–35].

In the earlier studies [17–19], it was found that bronchoscopic guidance reduces the risk of complications and is safe and cost-effective, but the recent comparative studies (although retrospective) have suggested that PDT can be safely performed without bronchoscopic guidance without any increase in complications and it is not mandatory to do bronchoscopy guided PDT [10–13]. Some authors have even hypothesized discarding the use of bronchoscopy for this procedure in order to potentially decrease its cost and increase its efficiency with similar outcomes compared with bronchoscopy-assisted PDT [10]. International guidelines [14] have not been able to establish a recommendation regarding this measure due to a lack of evidence. Therefore, the controversy surrounding the routine use of FB as part of PDT remains open.

The main difference between our study and other studies is that our study is the first prospective randomized clinical trial to assess this topic. All results about this topic are based on retrospective studies or case series. Should PDT be monitored routinely with endoscopic guidance? So far, there is no evidence to provide a definitive answer.

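### The blood-gas comparison names no baseline adjustment, does not say whether end value or change is compared, and lets the data choose the test; a pre-specified ANCOVA would be more precise at no cost

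*Protocol article*

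**What the plan says.** Three parts of the protocol article bear on this point.

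- **Data collection.** PaCO2, PaO2 and pH are each recorded twice; for pH the wording is "pH at the beginning and end of the procedure". Minimum SpO2 and maximum end-tidal CO2 are single values per patient.
- **Discussion.** Besides comparing the two techniques, the trial is meant "to evaluate the effects on ventilatory parameters during percutaneous tracheostomy with and without endoscopic control".
- **Statistical analysis plan.** One rule covers all quantitative variables: Student's "t test or the Mann-Whitney test, depending on the distributions of the variables analyzed". Tests are two-sided ("All tests will be considered two-tailed at a 95% level of significance"; "Statistical significance will be set at p<0.05"). The Kolmogorov-Smirnov test is named in the same section, for deciding between mean with SD and median with interquartile range.

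The section names no model with a baseline covariate. It does not define the variable to be compared for outcomes measured twice.

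**The concern.** A start value measured just before the intervention usually predicts the end value. An analysis that conditions on it removes that part of the between-patient variation from the treatment contrast. The stated rule does not do this.

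Two specification gaps come with it. First, end value and change are both compatible with the text, so an analyst could compute both and report either. Second, a t test contrasts means and Mann-Whitney contrasts ranks. If the observed distribution decides between them, the estimated quantity is not fixed in advance and may differ between PaCO2, PaO2 and pH.

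At stake is the precision and clarity of the ventilatory results. The sample size rests on complication rates, and the article shows no power calculation for the blood gases. A needlessly wide interval could be misread as showing that bronchoscopy has no ventilatory effect.

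**Working it through.** **The plan's own figure.** 221 per arm is for complications. The article quotes ranges of rates and no single design pair. Taking the lower ends, 3.7% and 11% (an assumption), the pooled two-proportion formula (two-sided 0.05, 80% power) gives 200 per arm. Allowing for 10% loss, this is 200/0.9 = 223 or 200 × 1.1 = 220, close to 221. The figure matters here only because it sets the number analysed: 221 × 0.9 ≈ 199 per arm.

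**Inputs for the blood gases**
- 199 analysed per arm, 1:1 allocation, two-sided 0.05 (from the article).
- Start-end correlation r: not in the article; assumed 0.3 to 0.8.
- Equal variance at start and end (assumed). The article gives no SD, so differences are in SD units.

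**Variance of the arm difference, relative to an end-value t test**
- End value: 1
- Change from start: 2(1 − r)
- ANCOVA: 1 − r²

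ANCOVA relative to the change score is therefore (1 − r²)/[2(1 − r)] = (1 + r)/2.

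| r | Change / end value | ANCOVA / end value | ANCOVA / change |
|---|---|---|---|
| 0.3 | 1.40 | 0.91 | 0.65 |
| 0.5 | 1.00 | 0.75 | 0.75 |
| 0.7 | 0.60 | 0.51 | 0.85 |
| 0.8 | 0.40 | 0.36 | 0.90 |

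Neither ANCOVA ratio exceeds 1, so the gain exists under either reading of the text. Its size depends on the reading. At r = 0.7, the end-value test would need 1/0.51 = 1.96 times the sample to match ANCOVA, but the change score only 1/0.85 = 1.18 times. At r = 0.3 the order reverses: 1/0.91 = 1.10 times for the end value, 1/0.65 = 1.54 times for the change.

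Interval width scales with the square root of variance. ANCOVA intervals are about 5%, 13%, 29% and 40% narrower than for end values at these four values of r, and about 19%, 13%, 8% and 5% narrower than for change scores.

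**Detectable difference at 80% power.** For the end value this is (1.960 + 0.842) × √(2/199) = 0.281 SD. The other methods multiply it by the square root of their variance factor.

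| r | End value | Change | ANCOVA |
|---|---|---|---|
| 0.3 | 0.281 | 0.332 | 0.268 |
| 0.5 | 0.281 | 0.281 | 0.243 |
| 0.7 | 0.281 | 0.218 | 0.201 |
| 0.8 | 0.281 | 0.178 | 0.169 |

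**Simulation check** (199 per arm, true effect 0.2 SD, normal data, 4000 runs). Power:

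| r | End-value t | Mann-Whitney on end value | Change t | ANCOVA |
|---|---|---|---|---|
| 0.5 | 0.52 | 0.50 | 0.51 | 0.63 |
| 0.7 | 0.52 | 0.50 | 0.73 | 0.80 |
| 0.8 | 0.51 | 0.49 | 0.89 | 0.92 |

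With log-normal data at r = 0.7 the values were 0.47, 0.50, 0.68 and 0.73, so ANCOVA still came first.

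**The case against.** The strongest reply is that an unadjusted two-sample comparison of a secondary variable in a randomised trial is valid, and that covariates for such variables are often settled in a fuller document. Validity is granted. But the article does not leave the method open: it states a rule for all quantitative variables, and that rule can be improved without new data.

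Several stronger readings are tempting and are not supported.

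- *The baseline is thrown away.* True only if end values are compared. A test on the change fits the wording equally well and uses the start value, though less efficiently than ANCOVA.
- *The sample is in effect halved.* That is roughly the loss at r = 0.7 for end values only. No correlation is given, and the loss is small for end values at r = 0.3 and for changes at r = 0.8.
- *Kolmogorov-Smirnov formally decides the between-arm test.* It is a fair inference, since no other normality check is named, but the article ties it by name only to the descriptive summary.
- *At this sample size a normality test rejects trivial departures.* Simulation with n = 199 does not bear this out. With the Lilliefors correction, rejection was about 14% for a t distribution with 10 df, 16% for skewness 0.3 and 39% for skewness 0.5; uncorrected, it was 2% or less. The case against data-driven selection is that the target stays open, whatever the rejection rate.
- *Chance baseline imbalance biases the result.* It adds noise, which the confidence interval already covers.
- *The plan expects bronchoscopy to cause hypercarbia.* The justification section lists it only as a possible risk.

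It also stands that the aim in the justification section and the primary outcome concern complications; ventilatory effects appear as an aim only in the Discussion.

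**Conclusion.** The point holds as one of efficiency and pre-specification for secondary outcomes. For blood gases measured at start and end, the stated rule leaves the compared variable and the type of contrast open and names no baseline adjustment. ANCOVA is more precise under either reading: across r from 0.3 to 0.8 its variance is 0.91 down to 0.36 of the end-value test's, or 0.65 up to 0.90 of the change-score test's. These ratios assume equal variances at start and end and a correlation that the article does not give, so the exact gain cannot be fixed. There is no bias, and neither the primary outcome nor the 221 per arm is affected. The change is worth making because the gain can be material and costs nothing.

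**What to change.** In the Statistical analysis plan section, take PaCO2, PaO2 and pH out of the general rule and specify, before the data are compared by arm:

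1. The outcome is the end-of-procedure value.
2. The analysis is ANCOVA with arm and the start value as covariate.
3. The result is the adjusted mean difference with its 95% CI.
4. Possible skewness is handled by a choice made in advance (the scale of analysis, or robust standard errors).
5. For these outcomes, the observed distribution does not choose the between-arm test.

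The descriptive use of the normality test can stay. The cost is a few sentences of text: the start values are already collected, and no change to the sample size is needed.
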